### Clinical Management and Pharmacogenetics Analysis

Patients in cohort 1 will receive the recently introduced PRINT program, an early intervention in psychosis model, including the 5SPM method based on pharmacogenetics developed by our unit of pharmacogenetics and precision medicine at the HUS. As mentioned previously, the 5SPM method includes five steps: (1) collection of clinical, epidemiological, and treatment data; (2) study of pharmacological interactions based on drug-specific pharmacokinetic pathways; (3) pharmacogenetic analysis of the genes that code enzymes involved in drug-specific metabolism; (4) introduction of or change in pharmacotherapy according to the data obtained in the previous 3 steps; and (5) analysis of the treatment outputs and reassessment if needed. These steps will be preceded by an informed consent process. This preliminary procedure plus steps 1 to 4 will be conducted as soon as possible, ideally when a patient with a first episode of psychosis is identified by clinical services, aiming to minimize the time between the initial presentation and pharmacogenetics-informed decisions on pharmacotherapy. Step 5 (treatment review) will be carried out 6 months after antipsychotic treatment initiation. All steps will require a multidisciplinary approach and a shared decision-making process including patients or their family or legal representatives, especially if the patient lacks the mental capacity to make such decisions.

For the pharmacogenetics analysis (step 3), we shall use mass spectrometry and real-time polymerase chain reaction to study the genes encoding enzymes 1A2, 2B6, 2C9, 2C19, 2D6, 3A4, and 3A5 of the CYP450 family, in addition to transporter ABCB1. The CYP450 superfamily contains highly polymorphic genes. The usual approach to the relationship between genotypic variability and the metabolism of CYP450 substrates is based on the definition of metabolic phenotypes with their characteristic pharmacokinetic implications according to different genetic mechanisms. Metabolic profiles will be considered to make decisions on antipsychotic treatment choices. We already have enough technical support and pharmacogenetics evidence for most antipsychotics used in the early stages of a psychotic illness (ie, olanzapine, risperidone, paliperidone, quetiapine, aripiprazole, amisulpride, lurasidone, cariprazine, haloperidol, and zuclopenthixol).

Cohort 2 will have received standard care provided by mental health services before the PRINT program implementation, specifically by mental health professionals working in generic community mental health teams that offer assessment and treatment to people who reside in their geographical catchment areas and experience a wide range of mental disorders, not only psychotic disorders.

### Patient and Public Involvement

Patients have been involved in the design and will participate in the delivery of this trial. For instance, patients with first-episode psychosis were consulted on the feasibility of running this project, and some of them were involved in its design, specifically on what information to include in the informed consent form to carry out the pharmacogenetics analyses. In addition, we shall constitute a CLUMP patient and carer advisory group, which will also contribute to the identification of themes for the qualitative evaluation (see the Qualitative Evaluation section).

### Outcome Measures

#### Primary Outcome Measure

The primary outcome to measure treatment adherence will be all-cause discontinuation of the initially prescribed antipsychotic medication following the patient’s or treating clinician’s decision. All-cause discontinuation rates in the CLUMP project will be defined by all-cause discontinuation proportions during the 1-year follow-up and the mean time to such discontinuation.

For cohort 1, the 1-year follow-up period will start when an antipsychotic medication is prescribed taking into consideration the pharmacogenetics advice emerging from the 5SPM method. For cohort 2, follow-up would begin on the date when the first antipsychotic medication was prescribed. For both cohorts, the first prescribed antipsychotic will be the initially prescribed antipsychotic drug for maintenance treatment, not only for short-term use to control psychomotor agitation. In addition, in accordance with existing scientific consensus, the discontinuation date will be defined as the first day of a 2-week or longer interruption of the first prescribed antipsychotic. In cohort 2, treatment discontinuation dates will be determined by examining clinical records. Where only approximate dates are available, the first, middle, or final day of the month will be used as best estimates. In cases in which cross-titration of medication took place, the date of discontinuation will be the first day of the cross-tapering process.

All-cause discontinuation will also be stratified by 4 reasons: insufficient efficacy, adverse events, lack of adherence, and other. Insufficient efficacy will be established at the treating clinician’s judgment only after at least 3 weeks of treatment. If more than one reason for discontinuation was present, we shall select one by applying the ranking order as stated previously.

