### Statistical Analysis

Comparisons of the main outcome (ie, discontinuation rates) will be carried out using the chi-square test. Kaplan-Meier survival curves and multivariate log rank tests will be used to assess time to all-cause antipsychotic discontinuation. For these analyses, patients will be followed up on for a year, from antipsychotic treatment initiation until discontinuation. Thus, we shall censor survival time by the end of the 1-year observation period or before such date if there is enough evidence of antipsychotic discontinuation. We shall describe and compare sociodemographic information and clinical and functional outcomes within and between groups. Means and SDs will be used to describe quantitative variables. We shall use the chi-square test or Fisher exact test for categorical variables and Mann-Whitney *U* test for continuous variables, among others. Data analyses will be conducted using the R statistical software (version 4.4.2 for Windows).

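### The two cohorts start the one-year clock at different points, so for cohort 1 patients already on maintenance treatment an early stop or switch can go uncounted while a comparable one in cohort 2 counts

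*Protocol article*

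**What the plan says.** The section Primary Outcome Measure sets two origins. In cohort 1 "the 1-year follow-up period will start when an antipsychotic medication is prescribed taking into consideration the pharmacogenetics advice". For the comparator: "For cohort 2, follow-up would begin on the date when the first antipsychotic medication was prescribed".

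The same section defines the index drug once: "For both cohorts, the first prescribed antipsychotic will be the initially prescribed antipsychotic drug for maintenance treatment", leaving out drugs used only briefly for agitation. An event is dated by two rules that carry no cohort limit: "the discontinuation date will be defined as the first day of a 2-week or longer interruption of the first prescribed antipsychotic", and, where one drug is cross-titrated to another, "the date of discontinuation will be the first day of the cross-tapering process".

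Statistical Analysis gives a single origin without separating the cohorts: "patients will be followed up on for a year, from antipsychotic treatment initiation until discontinuation". Economic Evaluation likewise sets a one-year horizon from antipsychotic initiation in both cohorts.

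Clinical Management and Pharmacogenetics Analysis describes step 4 of the 5SPM method as "introduction of or change in pharmacotherapy according to the data obtained in the previous 3 steps". On the timing of consent and the first four steps, it says that they "will be conducted as soon as possible, ideally when a patient with a first episode of psychosis is identified by clinical services". No maximum delay is given. The article does not say how a discontinuation before cohort 1's time zero is handled.

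**The concern.** Take a cohort 1 patient who starts a maintenance antipsychotic before the pharmacogenetic result is available. By the shared definition, that drug is the index drug. By the cohort 1 clock, follow-up begins at a later prescription, possibly of another drug. If the first drug is stopped before the advice, or replaced because of it, the event falls before or at time zero and drops out. In cohort 2 an early stop or switch of the first maintenance drug is always inside the observation window.

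This is delayed entry in one cohort only, on the primary outcome of a non-randomised comparison whose credibility depends on measuring that outcome in the same way in both cohorts. The Limitations section discusses a tendency to stay with the guided prescription, but not this. If it affects many patients, a lower discontinuation rate in cohort 1 could not be told apart from an effect of the clock.

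**Working it through.** **Inputs from the article (Effect and Sample Size).** Discontinuation 40% under existing care and 10% as the target; two-sided alpha 0.05; power 80%; dropout 0.2; 38 required and 50 planned per cohort.

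**The plan's own figure.** Arcsine effect size h = 2·asin(√0.4) − 2·asin(√0.1) = 0.726. n = 2·((1.960 + 0.842)/0.726)² = 29.8, rounded up to 30. 30/0.8 = 37.5, rounded up to 38. The stated number reproduces, so the issue is not the sample size arithmetic.

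**Assumptions not in the documents.** The share of cohort 1 treated before the advice, the delay to the advice, and the shape of the discontinuation hazard. Ranges are shown. In each case there is no true effect: 40% discontinue in both cohorts. False-positive rates come from exact enumeration of the uncorrected chi-square test with 50 per cohort. With no distortion this gives 5.2%.

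**(a) Uncounted switches among would-be discontinuers.** A share s of cohort 1 would have discontinued the first drug, is switched before time zero, and carries 40% risk on the new drug. Observed rate = (0.4 − s) + 0.4s = 0.4 − 0.6s.

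| s | Cohort 1 observed | Cohort 2 | False-positive rate |
|---|---|---|---|
| 10% | 34% | 40% | 9.5% |
| 20% | 28% | 40% | 24% |
| 30% | 22% | 40% | 50% |

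**(b) Switches unrelated to who would discontinue.** Observed rate = 0.4(1 − s) + 0.4s = 0.40, so the comparison is not shifted.

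**(c) Delay only, same drug continued.** Patients still on the drug at week w are followed for a year from then. With cumulative hazard 0.511 at one year (−ln 0.6), Weibull shape k and t = w/52, the observed rate is 1 − exp(−0.511·[(1 + t)^k − t^k]).

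| Shape k | 4 weeks | 8 weeks | False-positive rate (4, 8 weeks) |
|---|---|---|---|
| 0.5 (strongly front-loaded) | 32.2% | 29.4% | 12.8%, 19.7% |
| 0.7 | 36.4% | 34.7% | 6.7%, 8.5% |
| 1.0 (constant) | 40% | 40% | 5.2%, 5.2% |
| 1.3 (rising) | 42.0% | 43.5% | 5.8%, 6.9% |

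Worked entry for k = 0.5, w = 8: t = 0.154; 1.154^0.5 − 0.154^0.5 = 0.682; 1 − exp(−0.511 × 0.682) = 0.294.

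**The case against.** The strongest reply is that the plan means the advice to come before the first maintenance prescription. The Introduction speaks of people never exposed to antipsychotics, and steps 1 to 4 are to be done as early as possible. The wording about a change in pharmacotherapy is generic to the 5SPM method and is not limited to antipsychotics. Where the intention is met, the origins coincide and no section conflicts with another. This stands as a limit on size: the documents permit the problem without saying how common it is. It does not remove the problem, because no maximum delay is set and no rule covers patients treated earlier.

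A second reply is that starting at the guided prescription is a recognisable choice, and that counting a report-driven change as a failure turns the intervention into an outcome event. That is a fair point about which question is asked. But cohort 2 has no matching origin, so the choice needs a landmark comparator, which the article does not provide.

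Several stronger readings are tempting and not supported:

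- A reader might infer that the first antipsychotic is defined differently by cohort. It is worded once, for both; it is the cohort 1 clock that fits it badly.
- A reader might infer that the bias always favours the intervention. Cases (b) and (c) show none under unrelated switching or a constant hazard, and a reversal under a rising hazard.
- A reader might call this immortal time. The time before the advice is left out, not credited to cohort 1 as event-free.
- A harsher model, in which switched patients take the reduced risk (0.4 − s)/(1 − s), gives 14% and an 84% false-positive rate at s = 30%. That is the extreme of one assumption.
- A reader might infer that events are sought in different sources, since clinical records are named for cohort 2's dates. The article is only silent for cohort 1, and Data Management lists record review for the whole project.

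**Conclusion.** The point holds in conditional form. The article states two time origins for one primary comparison. For any cohort 1 patient already on a maintenance antipsychotic when the advice arrives, the cohort 1 origin contradicts the shared index-drug definition and the origin used in Statistical Analysis and Economic Evaluation. Events before or at the advice are then lost in cohort 1 only.

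The distortion favours cohort 1 if discontinuation is front-loaded, or if the uncounted switches are among patients who would have discontinued. Its size depends on a share and a delay that the documents do not give: from nothing, when advice comes first or under case (b) or a constant hazard, up to an apparent 22% against 40% at the top of the range assumed here. Because a stated rule, and not merely a missing detail, can produce this on the primary outcome, it should be settled before the cohorts are compared.

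**What to change.** Reconcile Clinical Management and Pharmacogenetics Analysis, Primary Outcome Measure, Statistical Analysis and Economic Evaluation to one time zero and one index drug for the primary analysis:

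- Time zero in both cohorts is the date of the first maintenance antipsychotic prescription, whether or not the 5SPM advice was available.
- Record that date in cohort 1. Step 1 of the method lists current prescriptions, but the article does not say that the first prescription date is captured.
- Count stops and switches of that drug by the existing two-week and cross-taper rules in both cohorts.
- Report separately the discontinuations prompted only by the pharmacogenetic report.
- Keep the advice-informed start as a named secondary analysis, compared with cohort 2 patients still on their first drug at the same time since first prescription (landmark).

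The change is analytic: care and the required 38 per cohort stay as they are, and one date per cohort 1 patient is added. The price is a cohort 1 rate that may look less favourable. If the rate after advice is the targeted 10% and 10% or 20% of cohort 1 had an earlier stop or switch, the counted rate is 0.1 + 0.9 × 0.1 = 19% or 0.2 + 0.8 × 0.1 = 28%. Power against 40% with 50 per cohort then falls from about 95% to about 64% or 24%. These shares are again assumptions.

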### Participants

A total of 300 patients will be included in this project. We shall include 2 different cohorts. Cohort 1 will be a prospective sample of patients with first-episode psychosis referred over 18 months to the new early intervention in psychosis program of personalized precision psychiatry (PRINT) at CAUSA. Cohort 2 will be a retrospective, consecutive (in reverse chronological order as registered in the CAUSA electronic health records) sample of patients who experienced a first episode of psychosis before the implementation of PRINT.

Inclusion and exclusion criteria for both cohorts will be aligned with the PRINT program referral acceptance criteria, which are predominantly inclusive.

Inclusion criteria are as follows: patients (1) with a diagnosis of first-episode psychosis, either nonaffective or affective; (2) aged 12 to 35 years; and (3) followed by clinical services for at least 1 year or earlier if there was evidence of antipsychotic treatment discontinuation (see the Outcome Measures section). In addition, patients in cohort 1 or their family or legal representatives will have to provide written consent to take part in the CLUMP project, including pharmacogenetics analysis (see the Ethical Considerations section). For patients in retrospective cohort 2, this will not be an inclusion criterion, but all of them will be approached by our research team seeking their consent to obtain their pharmacogenetic profile for research purposes.

Exclusion criteria are as follows: patients (1) with first-episode psychosis due to organic causes, for example, brain diseases such as Huntington or Parkinson disease, HIV, syphilis, dementia, brain tumors or cysts, or brain injury; (2) with moderate to severe intellectual disability; and (3) who spent (cohort 2) or plan to reside during (cohort 1) most of the 1-year follow-up period in a locality out of the PRINT program’s catchment area.

For additional comparative purposes, we shall analyze the environmental, clinical, and pharmacogenetic information of patients with psychotic disorders of more than 5 years of evolution or with other mental disorders whose data are currently stored and have been ethically approved for research use in our unit of pharmacogenetics and precision medicine at the HUS.

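### In retrospective cohort 2 the index drug must be labelled maintenance or short-term from records that also show when it stopped, which leaves the primary outcome open to hindsight

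*Protocol article*

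**What the plan says.** The protocol article, under Primary Outcome Measure, identifies the drug to be followed by a rule that covers both groups: "the first prescribed antipsychotic will be the initially prescribed antipsychotic drug for maintenance treatment, not only for short-term use to control psychomotor agitation". It gives no criterion for deciding from a record which of the two a prescription was.

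The start of follow-up differs by cohort. In cohort 1, "the 1-year follow-up period will start when an antipsychotic medication is prescribed taking into consideration the pharmacogenetics advice emerging from the 5SPM method". In cohort 2 the wording is: "For cohort 2, follow-up would begin on the date when the first antipsychotic medication was prescribed".

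The sources differ too. Under Participants: "Cohort 2 will be a retrospective, consecutive (in reverse chronological order as registered in the CAUSA electronic health records) sample". Under Primary Outcome Measure: "In cohort 2, treatment discontinuation dates will be determined by examining clinical records".

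Two statements under Clinical Management and Pharmacogenetics Analysis bear on cohort 1. Consent and steps 1 to 4 of 5SPM "will be conducted as soon as possible, ideally when a patient with a first episode of psychosis is identified by clinical services", and step 4 is the "introduction of or change in pharmacotherapy according to the data obtained in the previous 3 steps". An antipsychotic may therefore already be in use, or have been stopped, before the cohort 1 clock starts.

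The outcome section also lists four reasons for stopping. Only insufficient efficacy carries a minimum treatment time (3 weeks); adverse events carry none.

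**The concern.** The maintenance label decides three things at once: which drug is assessed, when the year begins, and whether a stop counts. It depends on what the prescriber intended. In cohort 1 the index drug is the one prescribed with the 5SPM advice, so it is known before its outcome. In cohort 2 the person extracting the data works from a completed record. Where intent was not written down, how long the drug was used is an obvious clue to it, and duration is the outcome.

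Two errors become possible in cohort 2:

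- A drug meant as regular treatment but abandoned within days is read as short-term use. The next drug becomes the index drug and the first stop disappears. The control rate falls, against PRINT.
- A drug given only for agitation is read as the index drug, and its planned end is counted as a discontinuation. The control rate rises, in favour of PRINT.

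With about 50 patients per cohort, a handful of such decisions can move the primary comparison.

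**Working it through.** **1. Comparing the two cohorts**

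| | Cohort 1 | Cohort 2 |
|---|---|---|
| Start of follow-up | 5SPM-informed prescription | First antipsychotic prescription |
| When the index drug is identified | Prospectively | Retrospectively, from records |
| Later course visible when labelling | No | Yes, unless extraction is staged |
| How an early failure could be lost | Drug stopped before the 5SPM prescription | Drug read as short-term use |

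The article says only that cohort 2 stop dates come from clinical records. That the maintenance label comes from the same records follows from the retrospective design.

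**2. The plan's own figure**

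Effect and Sample Size uses rates of 40% and 10%, two-sided 0.05, 80% power and 20% dropout. With the arcsine effect size used by the R package it names:

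- h = 2·asin(√0.4) − 2·asin(√0.1) = 0.726
- n = 2·((1.960 + 0.842)/0.726)² = 29.8, rounded up to 30
- 30/(1 − 0.2) = 37.5, rounded up to 38, as stated.

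That section's list attaches 0.4 to cohort 1 and 0.1 to cohort 2, against its own narrative. I take 40% for cohort 2 and 10% for cohort 1; n is the same either way.

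**3. Early failures read as short-term use**

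Assumptions, none of them from the article: a share f of cohort 2 stops is relabelled, and the replacement drug is stopped within its year with probability q = 0.40. The observed rate is 0.40(1 − f) + 0.40·f·q, so the fall is 0.40·f·(1 − q) = 0.24·f. Power is against 10% in cohort 1, with 50 × 0.8 = 40 evaluable per cohort.

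| f | Cohort 2 rate | Fall (points) | Power, pooled normal approximation | Power, arcsine |
|---|---|---|---|---|
| 0 | 0.400 | 0 | 0.89 | 0.90 |
| 0.1 | 0.376 | 2.4 | 0.84 | 0.86 |
| 0.2 | 0.352 | 4.8 | 0.78 | 0.80 |
| 0.3 | 0.328 | 7.2 | 0.71 | 0.73 |

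At the extreme q = 0 (no replacement drug is stopped), the fall is 0.40·f, or 4 to 12 points for f = 0.1 to 0.3, and pooled power is 0.80 to 0.54.

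**4. Agitation-only drugs read as index drugs**

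Assumption: a share g of cohort 2 patients who did not discontinue is recorded as having stopped. The rate becomes 0.40 + 0.60·g. The last column assumes no true difference (both rates 40%), 50 per cohort and the chi-square test without continuity correction, by exact enumeration.

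| g | Cohort 2 rate | Rise (points) | Chance of a significant result |
|---|---|---|---|
| 0 | 0.40 | 0 | 0.05 |
| 0.05 | 0.43 | 3 | 0.07 |
| 0.1 | 0.46 | 6 | 0.10 |
| 0.2 | 0.52 | 12 | 0.24 |

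**The case against.** The strongest reply is that the written rule turns on purpose, not duration. A drug stopped after days for side effects was not prescribed solely to control agitation, and the section counts adverse-event stops as discontinuations with no minimum time. Relabelling such a stop would misapply the rule, and so would counting an agitation-only drug. This stands: both errors are departures from the definition, and the article nowhere says that duration will be used. It does not remove the risk, because purpose has to be inferred where it was not recorded, and the inference is made with the stop date in view. The article itself expects imprecise cohort 2 records, since it allows stop dates to be set to the start, middle or end of a month.

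A reader might infer that early failures can be lost from the control cohort only. The documents do not support that. The rule covers both cohorts, and cohort 1 loses any drug stopped before its 5SPM prescription. Only hindsight labelling from records is particular to cohort 2.

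A reader might also infer a bias in a known direction, or one beyond remedy in the analysis. Neither follows. The two errors oppose each other, and a sensitivity analysis can show how much the choice of index drug matters.

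Finally, an extraction rule could sit in a fuller protocol that is not shown, and every share used in the arithmetic is assumed. Both points are fair. The article does, however, already fix rules for interruption, approximate dates and cross-titration; on the index drug it fixes a criterion of intent and two different start points.

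**Conclusion.** The point holds as a risk of hindsight labelling in cohort 2, arising from an intent-based definition applied to completed records while cohort 1 is anchored prospectively. It is not evidence that relabelling will occur.

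Direction and size cannot be determined from the article. If 10% to 30% of cohort 2 stops were relabelled and 40% of replacement drugs stopped, the control rate would fall by about 2 to 7 points and power at 40 evaluable per cohort would go from 0.89 to between 0.84 and 0.71. At the low end of that range power stays above the planned 80%. The opposite error, in 10% to 20% of non-discontinuers, would raise the control rate by 6 to 12 points and the chance of a significant result without a true difference from 0.05 to between 0.10 and 0.24.

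The different start points are a separate, stated asymmetry through which cohort 1 can also lose early failures. A modest change to data extraction is warranted before cohort 2 records are abstracted.

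**What to change.** Keep the primary definition and both start points. Requiring the first scheduled antipsychotic as the index drug in both cohorts would conflict with the cohort 1 start, so that is not the remedy.

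1. In cohort 2, extract in two steps. First record the index drug and its start date using only entries up to the day of prescribing: documented purpose, and whether the order was scheduled or as needed. Only then read later entries for the stop date and reason.
2. State in the outcome definition that a drug ordered as regular treatment and stopped early counts as a discontinuation, however short its use.
3. Add one sensitivity analysis taking the first antipsychotic of any kind as index drug and time zero in both cohorts. This also shows the effect of the different start points. It needs the dates of any antipsychotic given before the 5SPM prescription in cohort 1.

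The cost is a two-step extraction form, a sentence in the definition and one extra analysis. In that analysis some agitation-only drugs will count as index drugs, so it should be read as a check on the primary result and not as a replacement for it.
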